**Figure 1 F1:**
[figure not shown]
Study flow chart.

### Assessments

This study will utilize both clinical and economical outcome measures (see Table 1). Assessments take place at baseline (before randomization), follow-up assessments are at post-intervention (6 to 8 weeks), and at 6 and 12 months after baseline.

**Table 1 T1:** Outcome measures

**Questionnaires**	**Aim**	**T0 Baseline (pre-test)**	**T1 Post-test (8 weeks)**	**T2 Follow-up I (6 months)**	**T3 Follow-up II (12 months)**
Primary outcome					
CES-D	Symptoms of depression	X	X	X	X
Secondary outcomes					
CIDI (Section E)	Diagnosis of depression	X	X		
HADS (Anxiety section)	Symptoms of anxiety	X	X		
ISI	Level of insomnia	X	X		
EQ-5D	Quality of life	X	X	X	X
Resource use					
F2F	Number of face-to-face appointments in MHC				X
TiC-P	General health service uptake and productivity losses	X	X	X	X
Mediator					
Mastery scale	Mastery	X	X	X	X
Moderators					
Demographic factors	User characteristics	X			
NEO-FFI (sections N + C)	Neuroticism and conscientiousness traits	X			
CAGE	Alcohol consumption	X			
CEQ	Expectancy and treatment	X			
AOCEQ	Expectations of the internet intervention	X			
CSQ-8	Client satisfaction with treatment		X		
AOCSQ	Satisfaction with type of intervention		X		

*AOCEQ* 'Alles Onder Controle’ Expectation Questionnaire, *AOCSQ* 'Alles Onder Controle’ Satisfaction Questionnaire, *CAGE* 'Cutting down, Annoyance by criticism, Guilty feeling, and Eye-openers’, *CEQ* Credibility/Expectancy Questionnaire, *CES-D* Center for Epidemiological Studies Depression scale, *CIDI* Composite International Diagnostic Interview, *CSQ-8* Client Satisfactory Questionnaire-8, *EQ-5D* EuroQol 5-Dimensions, *F2F* face-to-face, *ISI* Insomnia Severity Index, *HADS* Hospital Anxiety Depression Scale, *MHC* mental health center, *NEO-FFI* NEO-Five Factor Inventory, *TiC-P* Trimbos and iMTA Questionnaire on Costs Associated with Psychiatric Illness.

### Outcome measures

Our primary outcome will be symptoms of depression. Secondary outcomes are DSM-IV diagnosis of depression, number of face-to-face sessions in MHC, costs (in terms of all healthcare use and work absenteeism), anxiety, mastery, insomnia, quality of life, and satisfaction. Plausible moderators measured in this study will be alcohol use, personality, demographic factors and client expectations.

Because the Composite International Diagnostic Interview (CIDI) is part of the questionnaires at baseline and at post-intervention assessment (Table 1), the baseline questionnaires and the 6 to 8 week assessment will be administered by phone. Follow-up assessments at 6 and 12 months will be administered online. All questionnaires will be in Dutch.

### Primary outcome

#### Symptoms of depression

Symptoms of depression will be registered by using the Center for Epidemiological Studies Depression scale (CES-D) [17]. This scale consists of 20 items, the total score ranges between 0 and 60; higher scores indicate higher levels of depression and a score of 16 and above indicates a clinical level of depression. This questionnaire has been tested in various populations and has been found valid and reliable [18]. A Dutch version of the CES-D has been validated for internet administration [19].

### Secondary outcomes

#### Diagnosis of depression

The CIDI will be used to assess whether the DSM-IV diagnosis of depression has been met. The CIDI has been developed by the World Health Organization to assess DSM-IV Axis-I diagnoses [20]. For the purposes of this study, only section E will be administered, which allows for screening for depressive disorders. The CIDI will be conducted by phone by a trained interviewer.

#### Symptoms of anxiety

The subscale Anxiety of the Hospital Anxiety and Depression Scale (HADS) will be used to measure symptoms of anxiety. The depression scale will not be utilized in this research because depression will be measured by both CIDI and CES-D. The Anxiety subscale consists of 7 items, which scores range from 0 to 21; higher scores indicate higher levels of anxiety [21]. The HADS has shown to be reliable in Dutch populations [21].

#### Symptoms of insomnia

The perceived level of insomnia will be measured by the Insomnia Severity Index (ISI) [22]. This questionnaire measures both the concerns associated with the perceived level of insomnia, as well as symptoms and consequences of insomnia. Each item is rated on a 0 to 4 scale; a higher score indicates more severe insomnia. ISI has been found to be internally consistent and reliable [22].

#### Quality of life

The EuroQol 5-Dimensions questionnaire (EQ-5D), which consists of five items, will be used to measure quality of life. It registers the level of perceived problems (no, some or extreme) in five domains (mobility, self-care, usual activities, pain/discomfort and anxiety/depression). A total of 486 distinct health states can be scored which are located between 0, which indicates worst health possible, and 1, which indicates perfect health [23].

### Resource use

#### Costs related to the intervention

Costs related to the intervention will be calculated based on the costs of running the intervention in both conditions. To calculate costs related to the internet intervention, the costs of running the website platform and the costs of the hours of coaching invested in the intervention will be taken into account. Additional costs in the control group are the publishing of the self-help books.

#### Costs related to mental healthcare

Costs related to mental healthcare will be measured as the reported number and type of sessions by the MHC. This information is sent to the first author 12 months after participants have registered at the MHCs. The direct costs of the sessions will be calculated based on the Dutch standard cost prices [24].

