## Methods

### Study design

The study is a randomized controlled trial with an economic evaluation. We are currently enrolling 248 patients over 2 large mental health centers (MHCs) in 10 different locations. We will recruit patients directly after registration for regular face-to-face mental health services who need to wait for at least 6 weeks before their first treatment session. They will be randomized to either an internet-based guided self-help intervention or the regular waitlist before the first treatment session. People on the waitlist will receive a self-help book without additional guidance in order to motivate them to participate in the randomize, controlled trial (RCT). Both groups are allowed to receive regular face-to-face (FTF) therapy at the MHCs after the waitlist period. Participants in both groups complete assessment at baseline, at intervention or waiting list (WL) completion (6 to 8 weeks), at a 6-month follow-up, and at 12 months. The protocol of this study has been approved by the Medical Ethics Committee of the VU University Medical Center (registration number 2011/223).

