### Recruitment

Participants will be recruited while registering at the participating MHCs. In routine care patients are briefly scanned by the MHCs (according to MHCs protocol to screen out patients who are in crisis and need immediate treatment), and for the purpose of this study, patients with mood problems who are eligible for an intake assessment are asked by the MHC to share their contact details with the researchers. Those who are willing to do so, will then be called by a member of the research team who further explains the aim of this study and performs an additional check of the inclusion and exclusion criteria. If eligible, patients receive a study brochure and an informed consent form. Patients will only be included in the study if they meet all the criteria, and sign the informed consent form. In order to confirm the diagnoses Major Depressive Disorder trained interviewers conduct a clinical interview (CIDI).

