### Mental health centers characteristics

Two MHCs will be participating in this research. They each offer services at a number of different locations. In this trial, a total of ten locations will participate. These centers are chosen for pragmatic purposes, as they have a high number of patient enrolment, and have participated in prior research of the VU University. In general, patients are referred by their general practitioner to the mental health centers where the patients is screened and placed on a waiting list. Within 6 weeks an initial meeting with a therapist takes place in which the patient’s needs and preferences regarding to treatment are determined. At these participating MHCs it normally takes between 7 to 16 weeks for patients to have a first treatment session, depending on therapist workload, treatment modality and other factors. Treatment in both centers can consist of psychological therapies such as CBT, sometimes in combination with medication. The researchers are not involved in the face-to-face treatment, and neither in the decision-making process. However, prior to the start of this study all therapists at the participating MHCs will be informed about the goals of this study and the internet-based intervention, they will attend a Q&A session with the first author and receive the self-help book containing the intervention. Prior to the start of a patients’ face-to-face treatment at the MHC the therapists will be informed by the aforementioned note in electronic patient record and through email that their patients are participating in this study. One of the objectives of the internet-based intervention is that the subsequent face-to-face treatment can be adjusted to fewer sessions. The number and type of therapeutic sessions patients will receive is based on the needs of the patient, the judgment of the therapist, and protocol available at the MHC. The type and number of sessions will therefore vary per participant, and are outside the control of the researchers.

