### Randomization and blinding

The random allocation sequence will be generated by an independent researcher in the program 'Random Allocation Software’, stratified by location using blocks of six, eight and ten. After each inclusion another independent researcher will allocate the patient to either the intervention or the control condition. Due to the nature of the intervention the treatment group allocation cannot be concealed from the participants, nor from the research team and assessor of outcomes. Participants are assigned to one of two conditions within 2 working days from their baseline assessment Figure 1.

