#### Costs from a societal perspective

Healthcare costs in general as well as productivity losses will be measured with the revised version of the Trimbos and iMTA Questionnaire on Costs Associated with Psychiatric Illness (TiC-P). Direct costs will be measured by investigating which contact with health professionals has occurred and which type of medication has been prescribed. Indirect costs will be measured by work absenteeism and reduced productivity. The baseline TiC-P measures the care consumption 4 weeks prior to the intervention. The follow-up assessments at 6 and 12 months use a 14 and 26 weeks recall period respectively. Previous research has shown that up until half a year later, patients can reliably recall their consumption of health services [25]. The TiC-P has been used previously in a population with depressive symptoms in The Netherlands [26].

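### The MHC session report is timed from registration, but the session count, QALYs and other costs are timed from baseline, so the report closes before the 12-month assessment

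*Protocol article*

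**What the plan says.** Under Costs related to mental healthcare, the number and type of sessions come from the MHCs, and "This information is sent to the first author 12 months after participants have registered at the MHCs".

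The Assessments section uses a different origin: "follow-up assessments are at post-intervention (6 to 8 weeks), and at 6 and 12 months after baseline". Table 1 has a row for "Number of face-to-face appointments in MHC", marked only in the T3 (12-month) column. The 12-month CES-D, EQ-5D and TiC-P are in that same column.

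The order of events is clear. Study design says: "We will recruit patients directly after registration for regular face-to-face mental health services". Recruitment then describes several steps. Patients agree to share their contact details, and "Those who are willing to do so, will then be called by a member of the research team"; a brochure, signed consent and the diagnostic interview follow. Under Randomization and blinding, "Participants are assigned to one of two conditions within 2 working days from their baseline assessment". No section says how long the path from registration to baseline takes.

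**The concern.** The number of face-to-face sessions is a named secondary outcome. Aims and hypotheses makes fewer sessions the expected route to lower costs. Under Economic outcomes, the session costs enter a ratio with QALYs derived from the EQ-5D, which is measured from baseline to 12 months after baseline.

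If the session report is drawn 12 months after registration, it closes before T3. Sessions in the last weeks of the trial year are then missing from the outcome and from the MHC part of the costs, while the QALYs and the TiC-P costs run on to T3. If the MHCs also start counting at registration, the window is not only cut at the end but moved earlier. Mental health centers characteristics says of routine care: "Within 6 weeks an initial meeting with a therapist takes place". A count that starts at registration could therefore pick up a contact made before randomisation.

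**Working it through.** The protocol gives no figure for the gap, so there is none to reproduce. The sample size does not depend on this point.

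**Inputs**
- Report date: 12 months (52 weeks) after registration (Costs related to mental healthcare).
- T3: 12 months (52 weeks) after baseline (Assessments, Table 1).
- Wait to first treatment session, W: 7 to 16 weeks (Mental health centers characteristics; Control condition). I assume it runs from registration.
- Gap from registration to baseline, g: not stated. I assume 0 to 4 weeks.

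**Step 1: the two end dates.** Put registration at week 0. Baseline is at week g, the report at week 52, and T3 at week 52 + g. The report cannot cover (52 + g) − 52 = g weeks before T3. The two sections agree only if g = 0.

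**Step 2: share of possible treatment time lost.** Treatment can start at week W. The report can see 52 − W weeks, and a count to T3 needs 52 + g − W weeks. The share lost is g / (52 + g − W).

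| g (assumed) | W = 12 | W = 16 |
|---|---|---|
| 0 weeks | 0/40 = 0% | 0/36 = 0% |
| 1 week | 1/41 = 2.4% | 1/37 = 2.7% |
| 2 weeks | 2/42 = 4.8% | 2/38 = 5.3% |
| 4 weeks | 4/44 = 9.1% | 4/40 = 10.0% |

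**Step 3: how large the gap could be.** Control condition aims to keep MHC treatment from starting before the 8-week post-test. If that aim is met, W − g ≥ 8, so g ≤ W − 8. A wait of 8 weeks leaves no room for a gap. A wait of 12 weeks allows up to 4 weeks, which is why the table starts there. A wait of 16 weeks allows up to 8 weeks, and the loss would be 8/44 = 18.2%. With the post-test at 6 weeks, the limit at W = 16 is 10 weeks, or 10/46 = 21.7%. These are outer limits, not expected values.

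**The case against.** The strongest reply is that the protocol gives the date on which the information is sent, not the window over which sessions are counted, and that 12 months may be loose wording for the T3 time point. The text also suggests a short gap, since recruitment follows registration directly; at 0 to 1 week the loss is 0% to about 3%. This part stands as a limit on size. It does not remove the contradiction, because a report cannot contain sessions held after it was sent.

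It is also fair that calendar time is not sessions. A patient whose therapy has ended before the report date loses nothing, and the protocol gives no session schedule from which to compute the effect on the count or on the cost-effectiveness ratio.

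Four stronger readings are tempting, and the document does not support them:
- **That postponed sessions would look like avoided ones, favouring the internet arm.** This needs later therapy in that arm. Control condition says that participation does not alter waiting time. Registration precedes randomisation and allocation is stratified by location, so the cut falls on both arms equally in expectation. It could bias the difference only if late sessions differ by arm, and nothing in the text establishes that they do.
- **That MHC contacts would be counted twice.** The TiC-P section says "Direct costs will be measured by investigating which contact with health professionals has occurred and which type of medication has been prescribed", which may overlap with MHC records. No section says that the two sources are added together, and a rule for overlap is commonly left to the analysis plan.
- **That sessions are the main cost driver.** The protocol makes them the expected source of savings, but the societal analysis also includes other care, out-of-pocket costs and productivity losses. The TiC-P is timed from baseline, so only the record-based part is affected.
- **That intake contacts before randomisation distort the comparison.** The start of the count is not defined, the MHCs report the type of session, and such contacts would be balanced by randomisation.

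**Conclusion.** The point holds as a contradiction between two stated dates. Followed as written, the rule under Costs related to mental healthcare closes the session record before the T3 date that Table 1 assigns to it. The session outcome and the MHC-record costs then cover a shorter or shifted period compared with the QALYs and the other costs.

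The size is uncertain and probably modest: 0% to about 10% of possible treatment time for a gap of 0 to 4 weeks. This rests on the assumed gap and on a wait counted from registration. It shows no bias in favour of either arm and no known error in the session count. It is worth correcting because the outcome carries the cost hypothesis and the correction is cheap.

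**What to change.** Reconcile Costs related to mental healthcare with Assessments and Table 1. Ask the MHCs for sessions with their dates, extract them after each participant's 12-month (T3) date, and count those from randomisation (or baseline) to 12 months in both arms.

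The cost is an extraction later by the length of the gap and a request for session dates. Patients carry no extra burden and the sample size is unchanged. Recruitment is still open according to Trial status, so the change can be made before the 12-month records of new participants fall due. Dated sessions would also show how long the gap was and how many sessions fell in it.

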#### Costs from a societal perspective

Healthcare costs in general as well as productivity losses will be measured with the revised version of the Trimbos and iMTA Questionnaire on Costs Associated with Psychiatric Illness (TiC-P). Direct costs will be measured by investigating which contact with health professionals has occurred and which type of medication has been prescribed. Indirect costs will be measured by work absenteeism and reduced productivity. The baseline TiC-P measures the care consumption 4 weeks prior to the intervention. The follow-up assessments at 6 and 12 months use a 14 and 26 weeks recall period respectively. Previous research has shown that up until half a year later, patients can reliably recall their consumption of health services [25]. The TiC-P has been used previously in a population with depressive symptoms in The Netherlands [26].

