### Control condition

To increase participation rates in the control group, this group receives an unguided self-help book posted to their home address. This control group will not receive any feedback from coaches, nor will it have the opportunity to pose questions. Earlier research shows that self-help without any form of guidance only results in a small effect on participants with increased levels of depressive symptoms [16].

Participants in both conditions will be referred for regular FTF treatment after registration at the MHC. FTF treatment might consist of additional waiting time; the duration of the waiting time is highly variable with a minimum of 7 weeks and a maximum of 16 weeks depending on the location of MHC. Variation fluctuates both between locations and over time within the centers, due to availability of therapists. In case the waiting time for any MHC falls below 8 weeks, new participants from this MHC will be temporarily excluded from participating in the research until the waiting time for new patients at this MHC exceeds 8 weeks again. This has been decided in order to not measure the effects of active treatment by the MHCs at the first post-intervention test at 8 weeks.

The researchers of this study do not influence the waiting time at the MHCs, nor will participation in this study influence the waiting time for the participants.

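### The 14-week TiC-P recall at 6 months does not reach back to the post-test, leaving 4 to 6 weeks of non-MHC care, medication and productivity loss in no recall window

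*Protocol article*

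**What the plan says.** The Assessments section times every visit from baseline: "follow-up assessments are at post-intervention (6 to 8 weeks), and at 6 and 12 months after baseline". Table 1 in that section gives the post-test as "T1 Post-test (8 weeks" and schedules the TiC-P at all four time points. The table describes the instrument's purpose as "General health service uptake and productivity losses".

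The section on costs from a societal perspective gives three recall lengths. For baseline: "The baseline TiC-P measures the care consumption 4 weeks prior to the intervention". For the later visits: "The follow-up assessments at 6 and 12 months use a 14 and 26 weeks recall period respectively". It gives none for the post-test. It supports long recall with this statement: "Previous research has shown that up until half a year later, patients can reliably recall their consumption of health services".

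Treatment at the MHCs has its own source, in the section on costs related to mental healthcare: "Costs related to mental healthcare will be measured as the reported number and type of sessions by the MHC". The centers send this information 12 months after registration.

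The Economic outcomes section commits to a societal perspective that includes productivity losses.

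**The concern.** A 12-month cost total built from recall questionnaires needs windows that meet. Each one should begin no later than the previous assessment. The 12-month window meets the 6-month visit. The 6-month window does not appear to reach the post-test, and a questionnaire given at the post-test cannot cover weeks that have not yet happened.

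At stake is the economic evaluation, which is named in the title and is a stated aim. The uncovered weeks come shortly after a 5-week intervention, when a difference between arms in work absence, GP contacts or medication is plausible. The protocol gives no other source for those items. Bootstrapping describes sampling uncertainty and says nothing about weeks that no participant was asked about. The planned imputation is for missing endpoints, which is a different problem from an interval left out for everyone. A larger sample does not help, and once a participant has passed the 6-month assessment the information cannot be recovered directly.

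**Working it through.** **Inputs**
- Post-test: week 6 to 8 (Assessments); week 8 in Table 1.
- Follow-up: 6 and 12 months after baseline (Assessments).
- Recall: 14 weeks at 6 months, 26 weeks at 12 months (Costs from a societal perspective).
- Assumption: 6 months = week 26 and 12 months = week 52. A 24-week reading of 6 months is also tried.

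**Formulas**
- Window start = assessment week − recall length.
- Gap = window start − week of the previous assessment.

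**12-month visit, as a check on the calendar**
- Window start = 52 − 26 = week 26; gap = 26 − 26 = 0.
- The stated 26 weeks therefore fits the schedule exactly, which supports reading half a year as 26 weeks.

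**6-month visit**
- Window start = 26 − 14 = week 12.
- Post-test at week 8: gap = 12 − 8 = 4 weeks; 4/52 = 7.7%.
- Post-test at week 6: gap = 12 − 6 = 6 weeks; 6/52 = 11.5%.

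**Sensitivity to the calendar: 6 months = 24 weeks**
- Window start = 24 − 14 = week 10.
- Gap = 10 − 8 = 2 weeks, or 10 − 6 = 4 weeks.

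**What would make 14 weeks fit**
- With the post-test as stated, the 6-month visit would have to fall at week 6 + 14 = 20 to week 8 + 14 = 22.
- With the 6-month visit at week 26, the post-test would have to fall at week 12.
- Neither matches the schedule.

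**Recall needed to close the gap**
- 26 − 8 = 18 weeks to 26 − 6 = 20 weeks. On the 24-week reading, 16 to 18 weeks.
- All are shorter than the half-year (about 26 weeks) that the protocol accepts as reliable.

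**Which cost items fall in the gap**

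| Item | Stated source | Affected? |
|---|---|---|
| Number and type of MHC sessions | Reports from the MHC | No |
| Health contacts outside the MHC | TiC-P | Yes |
| Medication | TiC-P | Yes |
| Absenteeism and reduced productivity | TiC-P | Yes |

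**The case against.** The strongest objection concerns scope. A reader might infer that all healthcare use in these weeks is lost, including the start of face-to-face treatment, since the Control condition section puts the wait at "a minimum of 7 weeks and a maximum of 16 weeks" and that range overlaps the gap. The protocol does not support this. Session counts come from the centers and do not depend on recall. The protocol's own cost hypothesis, fewer regular sessions in the internet group, is therefore not touched. This part of the objection stands and limits the point to TiC-P-only items.

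A reader might also extend the loss to 8 of 52 weeks (15.4%) by supposing that the post-test form uses the 4-week baseline recall: 4 + 14 + 26 = 44 weeks covered. The protocol gives no post-test recall. A condensed article may leave that out, so the larger figure has no basis here. The 4 to 6 weeks do not depend on it.

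Third, the bias is conditional. The article does not say how costs are accumulated over time, and an analysis plan not shown might interpolate. This also stands: costs are understated only if windows are simply added, and incremental cost is biased only if the arms differ during the gap. But interpolation only substitutes an assumption for data that a longer recall would supply.

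Finally, 14 weeks may be a misprint rather than what the form asks. The document cannot settle that. Either way the stated figure and the stated schedule disagree and must be reconciled.

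**Conclusion.** The point holds for costs measured only by the TiC-P. As written, the recall at 6 months and the visit schedule are inconsistent, and no post-test time within the stated range reconciles them. The uncovered time is 4 to 6 weeks if 6 months is 26 weeks, and 2 to 4 weeks if it is 24.

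The percentages are shares of follow-up time. The share of cost lost, and the direction of any bias in incremental cost, cannot be derived from the protocol and should not be inferred from them. The CES-D primary outcome, the EQ-5D and the MHC session counts are unaffected.

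Correction is still warranted. The societal cost comparison is a main aim, the gap applies to every participant, and the trial was still recruiting when the article was written, so the right question could still be asked of those who had not reached 6 months.

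**What to change.** 1. Set the 6-month TiC-P recall to run back to the participant's own post-test (18 to 20 weeks), with that date printed on the form. Make the post-test recall reach back to baseline, and state both lengths in the protocol.
2. For participants already assessed on the 14-week form, declare the uncovered weeks. Fill them from the adjacent periods by one prespecified rule, the same in both arms, and add a sensitivity analysis that varies the filled-in costs.
3. If the form in use already covers the interval, correct the 14-week figure in the section on costs from a societal perspective. Nothing else is then needed for the 6-month form.

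The change needs no extra visits or patients. It does lengthen recall at 6 months by 4 to 6 weeks, which is 18/14 = 1.29 to 20/14 = 1.43 times the present length. That stays within the half-year limit, though the evidence the protocol cites for the limit concerns use of health services and not productivity loss. A change during recruitment also leaves two 6-month recall windows among participants, so the form version should be recorded for each. Interpolation from adjacent periods is weaker than direct recall where costs are changing, which is why it should be confined to those already assessed.
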